## Abstract

**Background:**

Patients with rheumatoid arthritis (RA) are at risk of developing interstitial lung disease (ILD), which is associated with high mortality. Screening tools based on risk factors are needed to decide which patients with RA should be screened for ILD using high-resolution computed tomography (HRCT). The ANCHOR-RA study is a multi-national cross-sectional study that will develop a multivariable model for prediction of RA-ILD, which can be used to inform screening for RA-ILD in clinical practice.

**Methods:**

Investigators will enrol consecutive patients with RA who have ≥ 2 of the following risk factors for RA-ILD: male; current or previous smoker; age ≥ 60 years at RA diagnosis; high-positive rheumatoid factor and/or anti-cyclic citrullinated peptide (titre > 3 x upper limit of normal); presence or history of certain extra-articular manifestations of RA (vasculitis, Felty’s syndrome, secondary Sjögren’s syndrome, cutaneous rheumatoid nodules, serositis, and/or scleritis/uveitis); high RA disease activity in the prior 12 months. Patients previously identified as having ILD, or who have had a CT scan in the prior 2 years, will not be eligible. Participants will undergo an HRCT scan at their local site, which will be assessed centrally by two expert radiologists. Data will be collected prospectively on demographic and RA-related characteristics, patient-reported outcomes, comorbidities and pulmonary function. The primary outcomes will be the development of a probability score for RA-ILD, based on a multivariable model incorporating potential risk factors commonly assessed in clinical practice, and an estimate of the prevalence of RA-ILD in the study population. It is planned that 1200 participants will be enrolled at approximately 30 sites in the USA, UK, Germany, France, Italy, Spain.

**Discussion:**

Data from the ANCHOR-RA study will add to the body of evidence to support recommendations for screening for RA-ILD to improve detection of this important complication of RA and enable early intervention.

**Trial registration:**

clinicaltrials.gov NCT05855109 (submission date: 3 May 2023).

## Background

Patients with rheumatoid arthritis (RA) are at risk of developing interstitial lung disease (ILD). The reported prevalence of ILD in patients with RA varies widely depending on the population studied and the criteria used to define ILD, with estimates ranging between 2% and 41% [1–6]. RA-ILD confers a substantially increased risk of mortality [4, 7–11]. A recent meta-analysis of data from 15 studies in patients with RA-ILD found a mortality rate of 49% over 5 to 10 years [12]. Patients with RA may also have other respiratory complications such as pleural disease [13], bronchiectasis [6, 14] or emphysema [6, 15].

The high mortality associated with RA-ILD means that it is important that it is detected and treated promptly. Indeed, a delay in the diagnosis of RA-ILD has been shown to be an independent predictor of mortality [16]. Early detection of RA-ILD would require screening of asymptomatic patients, as substantial lung damage and loss of lung function may occur before patients report respiratory symptoms such as dyspnoea [17–19] and respiratory symptoms may be underestimated in patients in whom joint disease impairs exertion. However, in an international survey of 354 rheumatologists conducted in 2019, 44% did not consider screening for RA-ILD to be necessary in patients with risk factors but no respiratory symptoms [20].

The gold standard for radiological assessment of ILD is a high-resolution computed tomography (HRCT) scan [21, 22]. Evidence is emerging on the use of lung ultrasound as a screening tool [23–27], but more data are needed to establish its accuracy in the detection of RA-ILD. The high prevalence of RA and lower prevalence of RA-ILD means that it would be inefficient and likely not feasible for all patients with RA to undergo HRCT, but there is no consensus as to which patients should be screened. Many factors have been associated with the development of ILD in patients with RA, including older age, male sex, smoking history, seropositivity for rheumatoid factor (RF) or anti-cyclic citrullinated peptide (CCP), elevated erythrocyte sedimentation rate (ESR), moderate or high RA disease activity, and the *MUC5B* promoter variant [3, 7, 28–33]. The risk of ILD appears to be similar in patients with RA taking different types of disease-modifying anti-rheumatic drugs (DMARDs) [34], although recent analyses have suggested a lower risk in patients taking tofacitinib compared with adalimumab [35] and in patients taking abatacept plus methotrexate compared with methotrexate alone [36]. The extent to which treatments for RA modify the risk of ILD, and whether any reduction in risk is due to better control of RA disease activity or to specific effects in the lung, remains unclear.

The *A*utoantibodies, *N*on-articular manifestations of RA, *C*igarettes, *H*e/him, *O*lder age at RA onset, *R*A high disease activity (ANCHOR)-RA study is a multi-national cross-sectional study that will develop a multivariable model for prediction of RA-ILD, which can be used to inform screening for RA-ILD in clinical practice. This study will also evaluate the prevalence of RA-ILD, features of RA-ILD on HRCT, and other pulmonary complications of RA, in patients with risk factors for RA-ILD. A sub-study will compare the performance of lung ultrasound and HRCT in the detection of ILD. This manuscript describes the design of the ANCHOR-RA study.

## Methods/design

### Study design and participants

The ANCHOR-RA study is a cross-sectional study that will be conducted at approximately 30 sites in the USA, UK, Germany, France, Italy, Spain. Eligible patients will be diagnosed with RA according to the 1987 American College of Rheumatology (ACR) [37] or the 2010 ACR/European Alliance of Associations for Rheumatology (EULAR) [38] classification criteria, with any duration of RA, and have ≥ 2 of the following risk factors for RA-ILD: male; current or previous smoker; age ≥ 60 years at RA diagnosis; high-positive RF and/or anti-CCP (titre > 3 x upper limit of normal); presence or history of certain extra-articular manifestations of RA (vasculitis, Felty’s syndrome, secondary Sjögren’s syndrome, cutaneous rheumatoid nodules, serositis, and/or scleritis/uveitis); high RA disease activity in the prior 12 months (Table 1). Patients will be excluded if they have previously been identified as having ILD, have had a chest CT in the prior 2 years, have received treatments known to induce ILD (e.g. radiation therapy to chest, bleomycin), have had a lung transplant, or have been diagnosed with an autoimmune disorder overlapping with RA, except secondary Sjögren’s syndrome. There is no restriction on the use of disease-modifying antirheumatic drugs (DMARDs).

**Table 1 Tab1:** Disease activity measures used to ascertain high RA disease activity in the ANCHOR-RA study

Measure	Range	High RA disease activity
PAS score [39]	0 to 10	≥ 8.0 to ≤ 10.0
PAS-II score [39]	0 to 10	≥ 8.0 to ≤ 10.0
RAPID-3 score [40]	0 to 10	> 4 to ≤ 10
CDAI score [41]	0 to 76	> 22.0
DAS-28-ESR or DAS-28-CRP [42, 43]	0 to 9.4	> 5.1
SDAI score [44]	0 to 86	> 26

CDAI, Clinical Disease Activity Index; DAS-28-ESR, Disease Activity Score with 28 joints using erythrocyte sedimentation rate; DAS-28-CRP, Disease Activity Score with 28 joints using C-reactive protein; PAS, Patient Activity Scale; RA, rheumatoid arthritis; RAPID-3, Routine Assessment of Patient Index Data 3; SDAI, Simple Disease Activity Index

Investigators will enrol consecutive patients from RA outpatient clinics using one of three methods: (1) they may contact consecutive patients from their clinic database to ascertain interest and screen them for eligibility; (2) they may conduct a search of their clinic database to identify patients who have ≥ 2 of the specified risk factors for RA-ILD and then contact consecutive patients in that group to ascertain interest and screen for eligibility, or (3) they may screen consecutive patients for eligibility and interest during routine clinic sessions.

The study will be carried out in compliance with the protocol, the principles laid down in the Declaration of Helsinki, and in accordance with the International Council for Harmonisation of Technical Requirements for Pharmaceuticals for Human Use (ICH), Harmonised Tripartite Guideline for Good Clinical Practice and Guidelines for Good Pharmacoepidemiology Practices. The Advarra Institutional Review Board has approved the study protocol (Pro00071380). All participants will provide written informed consent prior to entering the study. The study is registered on clinicaltrials.gov (NCT05855109; submission date: 3 May 2023).

### Data collection

Participants will undergo a volumetric HRCT scan using a standardised multi-detector row CT acquisition protocol at their local site. Visual assessment of scans will be conducted centrally by two expert radiologists. Imaging features on HRCT will be assessed according to established recommendations [21, 22, 45]. The presence/absence of ILD, free-standing bronchiectasis and emphysema will be adjudicated. Features related to these diseases will be assessed (Table 2). ILD will be defined as non-dependent abnormalities, including ground glass or reticular abnormalities, lung distortion, traction bronchiectasis, honeycombing, or non-emphysematous cysts. If there is disagreement between the radiologists regarding the presence or absence of ILD, bronchiectasis, or emphysema, a third expert radiologist will make the decision. HRCT scans will also be read by a local radiologist and incidental findings reported back to the investigator, as per standard of care.

**Table 2 Tab2:** Features on HRCT that will be assessed in the ANCHOR-RA study

Features related to ILD	Presence or absence of ILD (adjudicated)
	Presence or absence of: ground glass opacities traction bronchiectasis reticulations honeycombing
	CT pattern: usual interstitial pneumonia (UIP) non-specific interstitial pneumonia (NSIP) (cellular/fibrotic subtypes) lymphocytic interstitial pneumonia organising pneumonia (OP) diffuse alveolar damage respiratory bronchiolitis desquamative interstitial pneumonia, indeterminate
	Distribution of ILD: upper, middle or lower lung regions, or diffuse
	Predominance of ILD: upper, middle or lower lung regions, or diffuse
	Total extent of fibrosis to nearest 10%
	Total extent of ILD to nearest 10%
**Features related to bronchiectasis**	Presence or absence of free-standing bronchiectasis (adjudicated)
	Lobes involved
	Presence or absence of: mucus plugging bronchial wall thickening
**Features related to emphysema**	Presence or absence of emphysema (adjudicated)
	Distribution of emphysema: upper, middle or lower lung regions, or diffuse
	Extent of emphysema to nearest 10%

HRCT, high-resolution computed tomography; ILD, interstitial lung disease

Data will be collected prospectively on demographic and RA-related characteristics (including disease activity based on Disease Activity Score with 28 joints [DAS-28]), extra-articular features, comorbidities, pulmonary function and patient-reported outcomes (Table 3). The investigator will be required to start these assessments within 90 days of the participants providing informed consent and collect the data within a 90-day period. Participants can opt in or out of *MUC5B* promoter variant testing at a central laboratory and of biobanking of DNA, plasma and serum samples for future analyses.

**Table 3 Tab3:** Participant information to be collected prospectively in the ANCHOR-RA study

Demographics	Age
	Sex
	Height
	Weight
	Race/ethnicity
	Smoking status and pack/years
RA-related characteristics	Family history of RA
	Family history of ILD
	Duration of RA
	DAS-28
	Physician global assessment
	Presence of secondary Sjögren’s syndrome, Felty’s syndrome, vasculitis, ulcers, uveitis, scleritis, cutaneous rheumatoid nodules
	RA deformities such as ulnar deviation, subluxation, swan necking, boutonniere’s deformity
	Inflammatory markers (CRP, ESR)
Comorbidities and medications	Comorbidities
	Medications and doses
	Use of inhalants (never/past/current)
Respiratory-related assessments	Respiratory examination: presence of crackles, decreased breathe sounds, resting oxygen saturation, respiratory rate
	Spirometry (FVC in mL; FVC % predicted; FEV_1_ in mL; FEV_1_% predicted; FEV_1_/FVC ratio)
	DLco
	Environmental exposures (e.g. silica, asbestos)
	Previous COVID-19 infection
	HRCT (central read and local read)
Patient-reported outcomes (PROs)	RA-related PROs: MDHAQ [46] SF-36 [47] AA-VAS
	Lung-related PROs: mMRC dyspnoea scale [48] L-PF questionnaire [49] Presence of cough and dyspnoea: *“Do you have a cough that has been present for at least 8 weeks” (yes/no)* *“Do you have unusual shortness of breath that has been present for at least 8 weeks” (yes/no)* • Cough severity VAS (in participants who report cough)
Other	*MUC5B* promoter variant (for participants who opt in)
	DNA, plasma and serum biobanked samples (for participants who opt in)

The investigator will be required to start these assessments within 90 days of the participant providing informed consent and collect the data within a 90-day period

AA-VAS, Arthritis Activity Visual Analogue Scale; CRP, C-reactive protein; DAS-28, Disease Activity Score with 28 joints; DLco, diffusing capacity of the lung for carbon monoxide; ESR, erythrocyte sedimentation rate; FVC, forced vital capacity; FEV_1_, forced expiratory volume in one second; HRCT, high-resolution computed tomography; ILD, interstitial lung disease; L-PF, Living with Pulmonary Fibrosis; MDHAQ, multidimensional health assessment questionnaire; mMRC, modified Medical Research Council; RA, rheumatoid arthritis; SF-36, 36-Item short form survey; VAS, visual analogue scale

Data collected from medical records will comprise: age at RA diagnosis; previous treatments for RA; presence of erosions in hands on plain film radiography; disease activity based on the measures listed in Table 1 other than DAS-28 (remission/low/medium/high; first measures and last four measures); anti-SS-A/Ro antibody status; anti-SS-B/La autoantibody status; anti-nuclear antibody status and titres; RF status; anti-CCP status; and highest values and last four values for RF, anti-CCP, CRP and ESR.

### Outcomes

The primary outcomes will be the development of a probability score for RA-ILD, based on a multivariable model incorporating potential risk factors commonly assessed in clinical practice, and an estimate of the prevalence of RA-ILD and of radiological features of RA-ILD on HRCT in the study population.

Secondary outcomes will be the demographic and disease characteristics of participants with RA who do and do not have respiratory symptoms (cough and/or dyspnoea), the performance of the model in sub-populations with and without cough and/or dyspnoea, and correlations of pulmonary function tests and abnormal findings on auscultation with findings on HRCT.

Further outcomes include a multivariable model that additionally considers the *MUC5B* promoter variant as a potential predictor of RA-ILD. The performance of the model to predict RA-ILD defined using different extents of ILD and patterns on HRCT will be assessed in sensitivity analyses. The prevalence and HRCT features of free-standing bronchiectasis and emphysema will also be assessed.

### Model development and validation

Model development and validation will follow recommendations for diagnostic models [50]. Candidate risk factors for RA-ILD will be identified based on expert opinion, supported by a systematic literature search. A logistic regression model using least absolute shrinkage and selection operator (LASSO) penalisation will be fit with the full set of candidate predictors. The model may include a set of pre-specified terms to consider potential non-linear and interaction effects. The penalty parameter will be determined by a cross-validation procedure. The model will then be re-fit via classical maximum-likelihood methods with only those predictors with coefficients not set to zero in the first fit. Some predictors may be forced into the model following consultation with the steering committee. The overall performance of the model will be assessed using the Brier Score, Nagelkerke R² and adjusted Nagelkerke R². Discrimination will primarily be assessed using the area under the receiver operating characteristic (ROC) curve (c-statistic). Calibration will be assessed by a plot. Internal validation will be performed using a bootstrapping approach, which will be used to correct for over-optimism in the performance of the model. The ability of the model to identify participants who have RA-ILD on HRCT will be assessed by determining a cut-off for predicted probability (decision threshold). Participants with a predicted probability above the threshold will be classified as positive (i.e. as having RA-ILD) and participants with a predicted probability under the threshold as negative (i.e. as not having RA-ILD). Further performance measures (including sensitivity, specificity, positive and negative predictive values) of the model will be assessed. A similar process will be used to derive a model that additionally considers the *MUC5B* promoter variant. Reporting will follow the Transparent Reporting of a multivariable prediction model for Individual Prognosis or Diagnosis (TRIPOD) statement [51].

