### Sample size calculation

It is planned that up to 1200 participants will be enrolled. This sample size was calculated based on an assumed number of model parameters of 22 to 24, an assumed prevalence of RA-ILD in the study population (which is enriched for patients with RA-ILD) of 30%, an assumed c-statistic for the model of 0.75, and an assumed shrinkage factor associated with the predictors of 0.9 [52]. In this setting, the number of events per predictor parameter would be 15. A difference of 0.05 between the apparent and adjusted R^2^ of the model and a margin of error of 0.05 in estimating the risk of RA-ILD when the coefficients for all candidate predictors are set to zero is expected. After HRCT results from the first 600 participants are available, an interim analysis will be performed to determine whether the prevalence of RA-ILD in the study population will enable the modelling based on risk factors or if the sample size needs to be adjusted.

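### The final score is an unpenalised re-fit after LASSO, so the roughly 10% overfitting that the sample size anticipates stays in its coefficients

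*Protocol article*

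**What the plan says.** Under Model development and validation, the protocol article fits a LASSO logistic regression to all candidate predictors, with the penalty chosen by cross-validation. The final model is then defined: "The model will then be re-fit via classical maximum-likelihood methods with only those predictors with coefficients not set to zero in the first fit". The steering committee may force further predictors in.

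On checking, the section says "Calibration will be assessed by a plot". The next sentence assigns bootstrapping to internal validation and to correcting over-optimism in how the model performs. It does not say that the bootstrap result is applied to the coefficients or the intercept. Participants are then classified by a cut-off on predicted probability, and the *MUC5B* model is to be derived in a similar way.

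Under Sample size calculation, the article states "It is planned that up to 1200 participants will be enrolled", based on "an assumed number of model parameters of 22 to 24", a prevalence of 30%, "an assumed c-statistic for the model of 0.75" and "an assumed shrinkage factor associated with the predictors of 0.9". It reports 15 events per predictor parameter.

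Under Outcomes, the probability score is named first among the primary outcomes.

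**The concern.** LASSO does two things: it drops predictors and it pulls the remaining coefficients toward zero. Re-fitting the survivors by maximum likelihood on the same data keeps the first effect and undoes the second. The re-fitted coefficients are then, on average, too large for new patients. High predicted risks come out too high and low ones too low.

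Correcting the reported performance for optimism tells the reader how much this matters, but it leaves the equation that clinicians would use unchanged. The product is a probability, meant to help decide who is sent for HRCT. The accuracy of the probability itself is therefore at stake, beyond the ordering of patients.

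**Working it through.** **Inputs from the article (Sample size calculation).** N = 1200; p = 22 to 24 parameters; prevalence 0.30; c = 0.75; shrinkage factor S = 0.9; R² difference 0.05; margin of error 0.05.

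**Derived input.** The article gives no Cox-Snell R². Taking the linear predictor as normal within cases and non-cases, c = 0.75 and prevalence 0.30 give R² = 0.1604. The maximum is 1 − (0.3^0.3 × 0.7^0.7)² = 0.705.

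**Step 1: reproduce the plan's N.**

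- Shrinkage criterion: n = p / [(S − 1) ln(1 − R²/S)]. With S = 0.9, ln(1 − 0.1604/0.9) = −0.1963 and the denominator is 0.01963. So n = 22/0.01963 = 1121 and 24/0.01963 = 1223.
- R² criterion: S = 0.1604/(0.1604 + 0.05 × 0.705) = 0.820. The same formula then gives 561 to 612.
- Overall-risk criterion: (1.96/0.05)² × 0.3 × 0.7 = 323.

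The shrinkage criterion drives N, and 1200 lies within its range. Events per parameter are 1200 × 0.30 / 24 = 15.0, as stated. Solving the first formula for S at n = 1200 gives 0.906 (22 parameters) to 0.898 (24 parameters). In this formula S is the expected calibration slope of an unpenalised model with all candidate parameters.

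**Step 2: slope of the procedure as written.** Simulation with n = 1200, 24 candidates, true c = 0.75, 10-fold cross-validation, 60 replicates per setting, and slopes taken against true risks in 40,000 new patients. The effect patterns and predictor correlations are assumptions. Median slopes at 30% prevalence:

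| Effects | Full ML, 24 terms | LASSO kept (minimum-CV) | LASSO then ML re-fit (minimum-CV), with 10th–90th percentile | Re-fit after 1-SE penalty |
|---|---|---|---|---|
| dense | 0.874 | 0.936 | 0.874 (0.812–0.979) | 0.863 |
| mixed | 0.892 | 1.062 | 0.901 (0.824–0.994) | 0.926 |
| sparse | 0.880 | 1.130 | 0.922 (0.852–0.991) | 0.984 |

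A separate simulation used 12 binary and 12 continuous candidates with mild correlation and 40 repetitions per setting. It gave re-fit slopes of 0.905, 0.886 and 0.874 with 6, 12 and 20 true predictors. The two sets agree on about 0.87 to 0.92 for the minimum-CV penalty.

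**Step 3: what that does to a displayed risk.** Corrected logit = logit(0.30) + slope × [logit(displayed) − logit(0.30)], with logit(0.30) = −0.847.

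- Displayed 60%, slope 0.90: −0.847 + 0.90 × (0.405 + 0.847) = 0.280, which is 57%. At slopes of 0.87 and 0.92 it is 56% and 58%.
- Displayed 5%, slope 0.90: −0.847 + 0.90 × (−2.944 + 0.847) = −2.735, which is 6%.

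**Step 4: lower prevalence.** At an assumed 15%, the re-fit slopes are 0.794, 0.852 and 0.860 (dense, mixed, sparse), and the formula gives S = 0.86 to 0.85 for 22 to 24 parameters. Centred at logit(0.15) = −1.735, a displayed 30% becomes about 26% (slope 0.79) to 27% (slope 0.86).

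**Step 5: the missing step.** In the simulation that included a bootstrap, the re-fit slope was 0.883. Multiplying the coefficients by the bootstrap calibration slope moved it to 1.001.

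**The case against.** The strongest reply is that the two sections are consistent. N was chosen so that an unpenalised model would overfit by only about 10%, and the re-fit does about that. This stands. A reader might infer that the re-fit strips out shrinkage that the sample size depends on. The documents do not support that, because S = 0.9 describes an unpenalised model, so N = 1200 is not undermined. Nor does selecting first and re-fitting appear to cost more than fitting all 24 terms: the minimum-CV re-fit slopes (0.87 to 0.92) are close to those of full maximum likelihood (0.87 to 0.89).

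A reader might also infer that the calibration plot could not show the problem, since a maximum-likelihood logistic model has intercept 0 and slope 1 in its own data. That holds only for an uncorrected plot. The article does not say the plot is uncorrected, and the sentence that follows it plausibly extends the bootstrap correction to calibration. A corrected plot would show the problem, though it would still leave the coefficients as they are.

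The third reply is that the effect is small and hardly touches classification. Uniform shrinkage with a new intercept preserves the order of patients and the c-statistic. A cut-off derived from the model's own ROC curve would rescale with the score and select the same people. This also stands. What remains is the displayed probability, and any cut-off chosen for its meaning on the probability scale.

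Finally, simply publishing the LASSO coefficients is not a reliable alternative. The penalty rule is not stated, and under the 1-SE rule the kept LASSO coefficients gave slopes of 1.37 to 1.71, which is marked over-shrinkage.

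**Conclusion.** The point holds as an inexpensive improvement of modest size. The article makes an unpenalised re-fit the final model, gives the bootstrap only the task of correcting performance, and so leaves in the published coefficients the overfitting that its own sample size calculation anticipates. Under its assumptions the typical slope is about 0.87 to 0.92, with individual studies running from about 0.81 to 0.99. That is an overstatement of about 2 to 4 percentage points at a displayed 60%.

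This rests on assumed effect patterns and correlations, on a minimum-CV penalty, and on centring at the prevalence. With a 1-SE penalty the re-fit slope ranged from 0.86 to 0.98. The gap is larger if prevalence is lower. The 15% case is an assumption, and the interim analysis after 600 HRCT results is there to check prevalence and adjust N. The full protocol or analysis plan is not shown and may already specify the shrinkage.

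**What to change.** Add to Model development and validation, or confirm in the analysis plan:

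1. Repeat the whole procedure in each bootstrap sample: penalty choice, LASSO selection, any forced predictors, and the re-fit.
2. Multiply the re-fitted coefficients by the resulting bootstrap calibration slope and re-estimate the intercept. Publish that equation as the score.
3. Determine the decision threshold on these shrunken probabilities.
4. Report the optimism-corrected calibration slope with the calibration plot.
5. Do the same for the *MUC5B* model.

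The cost is a few sentences, a little more computation and slightly smaller published odds ratios. No extra participants are needed. For comparison, raising an unshrunk model's expected slope to only 0.95 would take about 2380 participants for 22 parameters (22/[0.05 × 0.1849]) or 2600 for 24, where 0.1849 = −ln(1 − 0.1604/0.95).

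### Calibration of the probability score is specified as a plot with no calibration statistic; an optimism-corrected intercept and slope should be added

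*Protocol article*

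**What the plan says.** The main outcome is a risk score: "The primary outcomes will be the development of a probability score for RA-ILD" (Protocol article, Outcomes). Under Model development and validation, a LASSO logistic model selects predictors, the selected model is re-fitted by maximum likelihood, and a cut-off on the predicted probability then classifies participants.

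That section goes through the performance domains in turn:

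- Overall: "The overall performance of the model will be assessed using the Brier Score, Nagelkerke R² and adjusted Nagelkerke R²".
- Discrimination: mainly the c-statistic.
- Calibration: "Calibration will be assessed by a plot".
- At the cut-off: sensitivity, specificity and predictive values, among others.
- Optimism: "Internal validation will be performed using a bootstrapping approach, which will be used to correct for over-optimism in the performance of the model".

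The section also commits to published recommendations for diagnostic models and to TRIPOD reporting. Outcomes lists as secondary "the performance of the model in sub-populations with and without cough and/or dyspnoea", without saying which measures that covers. Sample size calculation states "It is planned that up to 1200 participants will be enrolled" and rests on 22 to 24 parameters, 30% prevalence, a c-statistic of 0.75 and a shrinkage factor of 0.9.

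**The concern.** A cut-off on absolute risk works as intended only if the predicted risks are about right, so calibration is central to this product. It is also the one domain given a picture and no dedicated number.

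Two features of the plan make that weak. First, a model re-fitted by maximum likelihood has perfect average calibration and a slope of 1 in the data it was fitted to, so a plot in those data cannot reveal overfitting of the slope. Second, the sample size is driven by a shrinkage factor of 0.9, which is in effect an expected calibration slope, yet the slope is not named among the results. A reader could not check from the named measures whether the design target was met. Nor could a reader compare calibration between symptom groups other than by looking at two curves.

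**Working it through.** **Inputs.** From Sample size calculation: N = 1200, prevalence 0.30, c = 0.75, p = 22 to 24, shrinkage S = 0.9. Assumed: a binormal linear predictor, the mix of predictor effects in the simulations, and the size, prevalence and symptom frequency of the subgroups.

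**1. The plan's own figures.** Events per parameter = N × prevalence / p = 1200 × 0.30 / 24 = 15.0, as stated (16.4 with 22). From c = 0.75 and prevalence 0.30, the Cox-Snell R² is about 0.160. The shrinkage criterion is N = p / [(S − 1) ln(1 − R²/S)].

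- p = 22: N = 1122.
- p = 24: N = 1223, within 3% of 1200.
- The other two criteria need less: about 561 to 612 (R² difference of 0.05) and 323 (0.05 margin on overall risk).

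Shrinkage therefore determines the sample size, and the arithmetic is not in dispute.

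**2. Slope implied at N = 1200.** With p = 24 and S = 0.898: 24 / (0.102 × 0.1966) ≈ 1197. The expected slope in new patients is thus about 0.90 by the plan's own formula (about 0.906 with p = 22).

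**3. Slope in the development data.** Maximum likelihood solves Σ(y − p̂) = 0 and Σxⱼ(y − p̂) = 0 for every predictor. The first equation makes mean predicted risk equal observed risk. Together they give Σ(linear predictor)(y − p̂) = 0, so regressing the outcome on the linear predictor returns intercept 0 and slope 1. This holds however overfitted the model is.

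**4. Simulated slope in new patients** (n = 1200, 24 candidates, prevalence 30%, c about 0.75):

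| Setting | Mean slope | 5th–95th percentile | Share below 0.85 |
|---|---|---|---|
| LASSO then re-fit, 12 null candidates, 60 data sets | 0.88 | 0.77–1.01 | about 35% |
| Same setting, separate 60 data sets | 0.87 | 0.77–0.97 | 42% |
| 24 parameters by maximum likelihood, no LASSO | 0.87 | 0.78–0.97 | not computed |

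The bootstrap-corrected slope averaged 0.88 to 0.89 against a true mean of 0.90 with LASSO (30 data sets), and 0.87 against 0.87 without it. The correction recovers the average.

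**5. What a slope of 0.88 means.** Taking the 30% point as fixed, a predicted 10% corresponds to logit −0.847 + 0.88 × (−2.197 + 0.847) = −2.035, or 11.6%. A predicted 60% corresponds to −0.847 + 0.88 × (0.405 + 0.847) = 0.255, or 56.3%.

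**6. What the named numbers would show.** With c held at 0.75, the Brier score is 0.174 when calibrated, 0.174 at slope 0.9, 0.175 at 0.8 and 0.177 at 0.7. It is 0.178 when mean predicted risk is 35% against 30% observed. It moves little and shows neither direction nor form. The c-statistic does not move.

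**7. Precision of the added statistics** (large-sample 95% half-widths for a fixed score). Overall: slope ±0.15, observed/expected ratio 0.92 to 1.09. Symptom-free subgroup, assuming 30% to 70% of participants and prevalence 10% to 30%: slope from ±0.18 (n = 840, 30%) to ±0.40 (n = 360, 10%).

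**The case against.** The strongest reply is that the article condenses a fuller protocol and analysis plan that are not shown. It commits to recognised standards, and naming a plot does not rule out statistics beside it. That is right as far as it goes: a reader might infer that calibration will be judged by eye alone, and the text does not say so. But the section is not silent. It lists measures domain by domain and gives calibration a stated method without a statistic.

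A reader might also infer that the study will yield no number bearing on calibration. That is too strong. The Brier score has a calibration component, and predictive values give observed risk on either side of the cut-off. Suppose symptoms double the odds of ILD at a given score, are reported by 30–40% and are not in the model. At an assumed cut-off of 0.30, the positive predictive value would be 41–42% without symptoms and 58–60% with them. The groups would visibly differ, though these values do not measure calibration directly.

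A third inference is that patients without symptoms are the worst served, since the Background says "Early detection of RA-ILD would require screening of asymptomatic patients". The documents do not support it. Performance by symptom status is a planned secondary outcome, and calibration within it is left open. In the scenario above, predicted risk would be 29% against 24–26% observed without symptoms, and 31–32% against 39–41% with them. At an odds ratio of 1.5 the symptom-free gap is 2–3 points. But cough and dyspnoea are collected as yes/no items and the candidate list is not given. If a symptom indicator is kept in the re-fit, the gap in the development data is zero (25.5% against 25.5%, and 38.7% against 38.7%, in a check at n = 1200).

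Three further points stand. A smoothed curve can depart from the diagonal even when the slope is 1. A curve can itself be optimism-corrected. And a slope near 0.88 is close to what the design accepted; the corrected slope has not been shown to identify the particular data sets with the worst slopes.

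**Conclusion.** The point holds in a limited form. The article names a plot as the only dedicated calibration assessment, for a product whose use depends on absolute risk and whose sample size rests on a shrinkage factor of 0.9. With 24 parameters under the design assumptions, the expected slope in new patients is about 0.87 to 0.90, while the apparent slope is 1 by construction. The named scalar measures show that difference weakly or not at all. The lower end of the range depends on the simulated predictor effects; the upper end follows from the plan's own formula.

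The effect on individual risks is modest on average. This is a worthwhile improvement to a stated method; it does not show that the score will be wrong. Miscalibration by symptom status is conditional on symptoms not being predictors, and on odds ratios and frequencies that the article does not give.

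**What to change.** Replace the calibration sentence with wording such as:

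> We will examine calibration with a smoothed curve and with the calibration intercept and slope, each with a 95% confidence interval. Overall values will be corrected for optimism by repeating the entire procedure, LASSO selection and re-fit included, in every bootstrap sample. The intercept and slope will also be given separately by symptom status, as part of the planned secondary analysis.

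State how the intervals for the corrected values are obtained, because the half-widths above apply to a fixed score. Say in advance that the subgroup slopes will be imprecise (about ±0.18 to ±0.40 under the assumed sizes and prevalences), so that a wide interval is not read as evidence of good calibration.

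The cost is a few lines of code inside a bootstrap already planned, with no extra participants, data or change to the sample size. The drawback is that reported calibration may look less favourable than an uncorrected plot.
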